### Inclusion/Exclusion Criteria

Patients will be included based on the following criteria: adults who 1) are 18 years of age or older; 2) are members of either targeted Asian American or Latino American minority groups; 3) screen positive for symptoms of depression; and 4) are able to consent to study participation. Patients will be excluded if they have active unstable, untreated psychiatric illness precluding participation in the study (e.g., actively suicidal or homicidal or actively psychotic). Patients in the intervention arm will be excluded if they have bipolar disorder.

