### Recruitment strategy

All patients in participating primary care clinics will be offered screening for the symptoms of depression by the Patient Health Questionnaire-2 (PHQ-2) as part of their routine primary care visit [23]; data on age, gender, race, ethnicity and primary language will be obtained at the time of screening. Asian American and Latino American patients who screen positive for clinical depression will be called by study staff and invited to participate in the CFP consultation intervention. Patients also may be referred by participating PCPs. For the qualitative interviews, a subset of study participants will be invited to participate after the six-month follow-up visit, as well as eligible members of the target population who not participate in the study.

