### Six-month follow-up

Patients will have the option to complete the visit over the phone or in person. In both the intervention and usual care arms, patients will be given the QIDS-SR self-rated questionnaire and asked a brief "Resource Utilization Questionnaire" with questions regarding use of antidepressant medications, referrals/visits to mental health specialists, or alternative providers both in and out of the MGH system. The electronic medical record will also be reviewed at baseline and at the six-month follow-up for both intervention and usual care arms to obtain depression diagnoses, prescription of antidepressant medications, and referrals/visits to mental health specialists in the system.

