### Exploratory analysis

Descriptive analyses will be performed to provide information related to the study's experience conducting the initial screening patients within their primary care clinics.

Data from initial screens will be utilized to provide a greater description of the patient population at screening, recruitment and enrollment (e.g., race; ethnicity; preferred language; age; gender; level of depression (i.e., PHQ-2 score); service utilization, as well as identify which of these variables, if any, served to influence participation in the study. This information will allow us to describe, for example, whether consent to be contacted differs by level of depression and whether this is moderated by demographic factors (e.g., race, ethnicity, gender). Additionally we will provide additional data describing rates of enrollment as compared to the total screened.

Secondary exploratory analyses will explore the impact of the intervention on depression. Patients' scores on the QIDS-SR will be compared between the usual care and intervention arms. To measure changes in racial and ethnic disparities in depression recognition and treatment, rates of depression diagnoses will be compared from baseline to six-month follow-up for the intervention and usual care arms. As measures of the use of any ongoing specialty mental health care, the rates of prescription of pharmacotherapy and referrals/visits to mental health specialists as provided by patient self-report will be compared at baseline and at the six-month follow-up. Data analysis will be conducted using STATA statistical software [35].

A general linear model that accounts for clustering at the PCP level will be used. Analyses of the main outcomes will include as covariates any patient or physician factors that differed significantly between study arms. Outcomes regarding diagnosis and treatment will be assessed using general estimating equations with a binomial link and standard errors will be adjusted to account for clustering within practice. Separate analyses will be conducted for each outcome (i.e., dependent variables) -- changes in depressive symptoms, diagnosis of and treatment (prescription of antidepressant medications; referrals/visits to mental health specialists) for depression at six months after enrollment. The effect of study arm on each outcome will be assessed, controlling for significant differences emerging from the bivariate analyses.

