By improving the identification and treatment of depression in Latino American and Asian American populations, this intervention will help reduce the well-known problems with under-recognition and under-treatment of these minority patient groups. This CFP consultation service complements the current movement in psychiatry to enhance the treatment of depression in primary care settings, especially useful for minority patients who are unwilling or unable to access specialty mental health care.

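### Baseline diagnosis or treatment status is adjusted for in the six-month diagnosis and treatment models only if it differs significantly between arms; it should be a fixed covariate

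*Protocol article*

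**What the plan says.** **Who enters.** Under Inclusion/Exclusion Criteria, patients must be adults in a target group who "3) screen positive for symptoms of depression; and 4) are able to consent to study participation". For exclusions, "Patients will be excluded if they have active unstable, untreated psychiatric illness precluding participation in the study"; bipolar disorder is a further exclusion in the intervention arm only. No criterion concerns an existing depression diagnosis, current antidepressant use or current specialist care. Under Recruitment strategy, screening is offered to all clinic patients, and "Patients also may be referred by participating PCPs".

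**What is known at baseline.** Under Six-month follow-up, "The electronic medical record will also be reviewed at baseline and at the six-month follow-up for both intervention and usual care arms". That review covers depression diagnoses, antidepressant prescriptions, and in-system specialist referrals and visits.

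**What is analysed.** The Exploratory analysis section has two relevant parts:
- A descriptive part compares diagnosis rates from baseline to six months by arm, and self-reported treatment rates at the two time points.
- A modelling part takes as dependent variables the change in depressive symptoms and "diagnosis of and treatment (prescription of antidepressant medications; referrals/visits to mental health specialists) for depression at six months after enrollment". The binary outcomes use estimating equations with clustering-adjusted standard errors. Adjustment is limited to characteristics on which the arms prove significantly different.

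**The concern.** The purpose behind these outcomes is stated in the Discussion: "this intervention will help reduce the well-known problems with under-recognition and under-treatment of these minority patient groups". A patient with a chart diagnosis of depression at entry will usually still have one six months later, in either arm. Baseline status is therefore likely to be among the strongest predictors of six-month status, yet the adjustment rule lets it into the model only after a significance test.

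Two things follow. First, a chance imbalance too small to reach significance goes unadjusted and appears in the modelled six-month arm difference. Second, even when the arms are balanced, patients whose status is already settled add variance and shrink the arm difference. The article says the exploratory results will inform later versions of the intervention and design, so a distorted or needlessly imprecise estimate would be carried forward.

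**Working it through.** The documents give no figure for the diagnosis and treatment outcomes, so there is none to reproduce. The original power statement (506 patients, 84%) concerns the QIDS-SR and does not bear on this point.

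**Inputs.** 60 per arm comes from Sample size and power (120 in total, split evenly). Everything else is assumed: the share already diagnosed, f; new diagnosis among the undiagnosed of 20% (usual care) and 40% (intervention); everyone diagnosed at baseline stays diagnosed; clustering ignored.

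**1. Imbalance with no true effect.** Suppose 20/60 and 29/60 are already diagnosed, and 20% of the rest are newly diagnosed in both arms.
- Baseline test: difference 0.483 − 0.333 = 0.150; SE = √((0.222 + 0.250)/60) = 0.0887; z = 1.69. This is not significant at the two-sided 5% level, so no covariate is added.
- Six-month rates: (20 + 0.2×40)/60 = 28/60 = 46.7%, and (29 + 0.2×31)/60 = 35.2/60 = 58.7%.
- Spurious difference: 12.0 points, which is 0.15 × 0.8.
- On change from baseline, the same data give 8/60 = 13.3% and 6.2/60 = 10.3%. Subtraction removes most of the distortion and leaves 3 points in the opposite direction.

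**2. Precision when the arms are balanced.** With share f already diagnosed, arm rates at six months are f + (1−f)p, so the arm difference is (1−f)(p₁−p₀). In each case z = difference/√((p₀q₀ + p₁q₁)/n), using the rates and n that apply.

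For f = 40%:
- Raw six-month comparison: 52% v 64%, n = 60; z = 0.12/√((0.2496 + 0.2304)/60) = 0.12/0.0894 = 1.34.
- Change from baseline: 12% v 24%, n = 60; z = 0.12/√((0.1056 + 0.1824)/60) = 0.12/0.0693 = 1.73.
- Undiagnosed at baseline: 20% v 40%, n = 36; z = 0.20/√((0.16 + 0.24)/36) = 0.20/0.1054 = 1.90.

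The information ratio is the squared ratio of z values:

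| f | z raw | z change | z undiagnosed | undiagnosed v raw | undiagnosed v change |
|---|---|---|---|---|---|
| 20% | 1.79 | 2.09 | 2.19 | 1.5 | 1.1 |
| 40% | 1.34 | 1.73 | 1.90 | 2.0 | 1.2 |
| 60% | 0.98 | 1.36 | 1.55 | 2.5 | 1.3 |

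**3. Other rates.** The prior chart-review study described under Preliminary Studies had 18 of 38 patients (47%) with some action by the primary care provider. Setting 47% against an assumed 70%, with a two-sided 5% test, power in all 60 per arm is 57%, 42% and 27% at f = 20%, 40% and 60%. Among those without the outcome at baseline it is 63%, 51% and 36%. The direction is the same.

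**The case against.** The strongest reply is that the plan does not ignore baseline. The descriptive part compares rates from baseline to six months, which would show a pre-existing arm difference and largely subtract it. On that reading the loss of information at f = 40% is a factor of 1.2, not 2.0. Randomization scheme also matches practices on an index that includes the rate of diagnosed depression. Both points stand and limit the size of the problem. They do not remove it: the models that estimate the arm effect are worded for status at six months, and the matching uses 2007 practice-level rates, not the status of the roughly 120 patients enrolled.

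A reader might also infer that patients already in care cannot contribute, so that treatment outcomes should count new starts only. The documents do not support that. The treatment rates are presented as measures of ongoing specialty care. A patient on an antidepressant can gain a referral, and a treated patient can stop. Restricting to new starts would change the question. Moving treatment outcomes to the chart would also lose care outside the hospital system, which the self-report questionnaire captures.

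Nor can imbalance be called likely because clusters are few. The article gives four practices, each with several pods, but not the number of pods randomised.

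Finally, detail on exploratory outcomes is often left to an analysis plan. Here, though, the article itself fixes the rule for choosing covariates, and that rule is the fault.

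**Conclusion.** The point holds as a defect in a stated adjustment rule. A baseline variable that is likely to be strongly prognostic, and is already planned for collection, is left to a significance test. In the example, a non-significant baseline imbalance produces a false 12-point difference. With balanced arms and f between 20% and 60%, the raw six-month comparison carries 1/1.5 to 1/2.5 of the information available among the undiagnosed. If change from baseline is what is meant, the loss is only a factor of 1.1 to 1.3.

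These sizes rest on an assumed share already diagnosed, assumed rates of new diagnosis and no clustering. A reader might infer that the effect is masked altogether; the arithmetic shows only that it is scaled by (1−f). The outcomes are secondary exploratory, so the primary aim of feasibility, satisfaction and cost is not affected.

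**What to change.** In Exploratory analysis:
- For each diagnosis and treatment outcome, include the baseline value of that same outcome as a prespecified covariate, regardless of any significance test.
- Use the same source at both time points: the chart for diagnosis and the planned self-report for treatment, so that outside care is kept.
- Also report new diagnosis by six months among patients with no chart diagnosis at baseline. Make this the recognition analysis if nearly all patients diagnosed at baseline remain diagnosed, because the covariate would then predict the outcome perfectly.
- Keep all enrolled patients in the treatment analyses, and show new starts and continuation separately as supporting results.

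The cost is wording, plus a smaller denominator in the new-diagnosis analysis. One item needs confirming. Table 1 schedules the Resource Utilization Questionnaire at baseline without an intervention-only mark, while Baseline Visit names only the QIDS-SR and SOS-10 for usual care. Baseline self-report of treatment must be collected in both arms for the treatment adjustment to work.

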## Discussion

The intervention is designed to provide enhanced recognition and treatment of depression in Asian American and Latino American primary care patients, while placing minimal additional burden on the existing primary care system at MGH. Several challenges to the implementation of this intervention exist, including minimizing burden to participating sites, recruitment and retention issues, and language and literacy issues.

Regarding the first challenge, obtaining staff and partnership buy-in during the grant-writing stage, and soliciting feedback from all levels of administration during every step of the process of designing and implementing the study has been instrumental. Regular meetings with participating sites are crucial to clarify workflow, questions about the service, and other issues that may arise. Keeping the protocols simple and easy to implement will be critical.

As with any clinical research intervention, recruitment and retention (e.g., dropout, loss to follow-up) are concerns (40). This is particularly relevant for recruitment and retention of minorities. Within recruitment and retention, the CFP team will consider how and which cultural issues are applicable in order to target Asian American and Latino American primary care patients. Among these groups, examples of such characteristics may include language and literacy, use of complementary and alternative treatments, the perceived importance of the quality of interpersonal relationships between the patient and CFP team, and the relationship between the PCP practices and the CFP team.

To address language and literacy issues, all materials (e.g., consent forms, study instructions) and the CFP consultations will be provided in the patient's preferred primary language, and materials for the toolkit will be developed at a sixth-grade reading level. The patient toolkit has also been prepared in audio CD format for patients with literacy issues. Recruiting research assistants and clinical staff with Spanish, Mandarin, Cantonese and Vietnamese proficiency are crucial to the team.

If patients and providers indicate strong satisfaction with the CFP intervention, it is hoped that the intervention can be expanded through a large scale randomized controlled trial of the intervention. Findings from such a study will provide evidence for the effectiveness of this model to improve the mental health of minorities in primary care settings.

Although this intervention is being piloted at MGH with Asian American and Latino American patients, the goal is ultimately to make it more generalizable with the ability to disseminate the intervention to different settings. To this end, a crucial end-product of this intervention will be the creation of a manualized "start-up guide" which will include the tools used to develop the CFP consultation, including conceptual models, protocols used for assessment, implementation process and its evaluation. A detailed evaluation will be conducted to understand the implementation process and costs (e.g., start-up and implementation). This implementation evaluation and cost analysis will inform the generalizability of this intervention. Organizations seeking to implement the CFP consultation intervention could use this guide to inform the development of an intervention appropriate to their setting.

Regarding dissemination, this consultation model could be used in any health care setting with outpatient clinics and sufficient staffing capacity to create a psychiatrically focused consultation service. Certainly, questions arise regarding the ability of an organization to implement this intervention with a significant minority population but few bicultural/bilingual providers, or in a setting where providers have not been trained to conduct similar culturally focused interventions. Such an organization may need concrete details regarding intervention implementation as discussed above. Similarly, the organization may benefit from seeking outside supervision and support from others experienced in conducting culturally focused interventions. However, such supervision and support is available and more readily accessible. One of the senior members of our team, [name], is an expert in the field of telepsychiatry and is currently developing a model of telepsychiatry consultation via the internet for Chinese American immigrants with depression. He is interested in eventually expanding a network of multicultural clinicians that can serve as consultants to patients in areas with underserved minorities, or as consultants to organizations planning to implement this model. The MGH CFP consultation team would be eager to serve in this capacity. If this intervention is disseminated to other organizations, further research regarding the generalizability and dissemination process of this intervention would inform this approach.

By improving the identification and treatment of depression in Latino American and Asian American populations, this intervention will help reduce the well-known problems with under-recognition and under-treatment of these minority patient groups. This CFP consultation service complements the current movement in psychiatry to enhance the treatment of depression in primary care settings, especially useful for minority patients who are unwilling or unable to access specialty mental health care.

## Conclusion

The proposed CFP intervention complements the current movement in psychiatry to enhance the treatment of depression in primary care settings. This project serves as a model for understanding both a) the effectiveness of improving the mental health care of minorities in primary care settings; and b) the feasibility of this intervention through the use of an implementation evaluation and cost analysis.
